### Data collection and follow-up procedures

All data will be recorded in an electronic Case Report Form (eCRF) specifically elaborated for the study (eCRF CleanWEB, Telemedicine Technologies S.A.S) and will be collected at four specific moments: upon randomization (V0), when performing the procedure (IVF or IUI) (V1), after the ultrasound at 6–7 weeks’ GA to confirm the clinical pregnancy (V2) and after a telephone call 12 months later for follow-up of women who had a clinical pregnancy confirmed at 6–7 weeks (V3). In the IVF group, the procedure (V1) will be divided into: V1a: day of oocyte retrieval, and V1b: day of embryo transfer. In the conversion to IUI group, data collection will be on the day of insemination (Fig. 1).

### Statistical analysis

We will perform a descriptive analysis of the population’s characteristics. Categorical variables will be expressed as numbers with percentages, and compared using Pearson’s chi-square test or Fisher’s exact test. Continuous variables will be reported as mean values and standard deviations, or medians with 25th and 75th percentile, and compared using Student’s *t* test or Mann-Whitney’s non-parametric test. All statistical tests will be bilateral and a *p* value < 0.05 will be considered statistically significant. We will perform an intention-to-treat and a per-protocol analysis of all outcomes. For the primary outcome, conversion to IUI will be considered non-inferior to IVF if the upper bound of the one-sided 95% confidence interval of the difference in LBRs between the two arms (the rate in IVF minus the rate in conversion to IUI) is ≤ 5%. Analysis of the primary and secondary outcomes will be adjusted according to the stratification variables used for randomization. The primary outcome will be tested using the raw difference in LBRs, and no complex model incorporating the stratification variables will be used. The dynamic randomization on these variables will ensure the variables are well-balanced. Subgroup analysis will be performed according to patients’ age (< 40 vs ≥40 years), the number of mature follicles (two vs three vs four) and patients considered poor ovarian responders according to the Bologna criteria. On the other hand, the cost-effectiveness analysis will be performed on an intention-to-treat basis (the hypothesis being that conversion to IUI is superior to IVF).

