### Trial design

This is a prospective, multicenter, parallel-group, open-label randomized controlled and non-inferiority trial conducted at 18 French departments of reproductive medicine (Table 1).

**Table 1 Tab1:** French partners of study

Gynecologists	Center/department
[name]	Coordinating investigator, Angers University Hospital, Angers
[name]	Nantes University Hospital, Nantes
[name] [name]	Caen University Hospital, Caen
[name]	Créteil University Hospital, Créteil
[name]	Rennes University Hospital, Rennes
[name]	Tours University Hospital, Tours
[name]	Strasbourg University Hospital, Strasbourg
[name]	Pointe-à-Pitre University Hospital, Guadeloupe
[name]	Lorient Public Hospital, Lorient
[name]	Clinique Jules Verne, Nantes
[name]	Polyclinique de l’Atlantique, Saint Herblain
[name]	Clinique de la Sagesse, Rennes
[name]	Clinique Pierre Cherrest, Neuilly-sur-Seine
[name]	Polyclinique Jean Vilar, Bruges
[name]	Clinique Léonard de Vinci, Chambray-lès-Tours
[name]	Grenoble University Hospital, Grenoble
Pr [name]	Marseille University Hospital, Marseille
Pr [name]	Antoine Béclère Hospital, Clamart

The study protocol was designed using the recommendations of the Consolidated Standards of Reporting Trial (CONSORT) Statement, Recommendations for Interventional Trials (SPIRIT) 2013 Checklist (Additional file 1) and according to the guidelines of cost-effectiveness studies of the French Health Authority. Eligible patients will be randomized equally to either conversion to IUI or IVF.

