### Recruitment

Patients will be recruited in all participating reproductive medicine centers across France. Potentially eligible patients will be pre-identified by the investigator or the co-investigators, based on their medical files and the different selection criteria that can be evaluated at the time, without informing these patients. Patients will be identified during ultrasound monitoring of follicular growth in the course of COS, and those with POR will be handed an information letter explaining the study protocol, so that they are already fully informed by the time they reach ovulation trigger day. The inclusion visit will take place on the day the decision to trigger ovulation is taken. During the inclusion visit, the investigator will thoroughly explain the study and hand the patient an information letter, written in an easily accessible language. The patient who wishes to be enrolled will sign the consent form, and will be randomized to one of the two groups. Randomization will be performed centrally by the trial coordinators using an online randomization module (Ennov Clinical®) in a 1:1 allocation ratio between IVF and conversion to IUI, as shown in Fig. 1. Moreover, randomization will be dynamic, and stratified by: center, number of mature follicles (two, three or four) and age (< 40 or ≥ 40 years).

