### Study population

At our center, in 2014, we performed 30 IVF cycles following COS with high doses of gonadotropins (≥ 300 IU) in patients at risk of POR. Our clinical pregnancy rate (CPR) was 10% (3/30), and our LBR was 10% (3/30). During that same year, we had 37 IVF cycles which were converted to IUI because of POR. The CPR was 11% (4/37) and LBR was 5% (2/37). If we consider that a maximal difference of 5% between IVF and conversion to IUI is clinically acceptable in order to consider conversion to IUI to be non-inferior to IVF, we will need to include 940 cycles, 470 in each group, to confirm the non-inferiority, with a power of 80%, an α risk of 5% and with 5% of non-evaluable cycles. It is worth noting that patients who are excluded from the study for failure of treatment can be included later on during their next IVF cycle, considering they still fulfill the inclusion criteria.

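### The plan calls the primary analysis both adjusted for the stratification variables and a raw difference, and does not say which one is held against the 5% margin

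*Protocol article*

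**What the plan says.** The Recruitment section of the protocol article states that "randomization will be dynamic, and stratified by: center, number of mature follicles (two, three or four) and age" (under 40, or 40 and over). The Trial design section describes an open-label "non-inferiority trial conducted at 18 French departments of reproductive medicine".

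In the Statistical analysis section, conversion to IUI is declared non-inferior "if the upper bound of the one-sided 95% confidence interval of the difference in LBRs between the two arms" (IVF minus conversion to IUI) is no more than 5%. Two sentences on how the primary outcome is analysed then follow one another:

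- One promises adjustment for every outcome level: "Analysis of the primary and secondary outcomes will be adjusted according to the stratification variables used for randomization".
- Its successor withdraws that for the main comparison and sets out an unadjusted test instead: "The primary outcome will be tested using the raw difference in LBRs, and no complex model incorporating the stratification variables will be used".

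The reason given for the second is that "The dynamic randomization on these variables will ensure the variables are well-balanced".

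The Study population section sets the margin ("a maximal difference of 5% between IVF and conversion to IUI is clinically acceptable") and plans 940 cycles, 470 per arm, for 80% power, an alpha of 5% and 5% non-evaluable cycles.

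**The concern.** The adjustment sentence names the primary outcome expressly. The next sentence takes the adjustment away from that same outcome. The decision rule does not settle the matter, because it refers to the difference in live birth rates without saying whether that difference is raw or adjusted. No other section ranks the two analyses.

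The trial's conclusion is one threshold crossing: a single upper bound against 5 percentage points. If the raw and adjusted bounds fall on opposite sides of 5%, the protocol as written supports either verdict. Treatment is open-label, so the protection against choosing between analyses after seeing results has to come from the text. This is not a detail left to a later analysis plan. The document fixes the primary analysis twice, in two incompatible ways, and an analysis plan faithful to one sentence departs from the other.

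**Working it through.** **1. Which analysis does the sample size assume?**

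Inputs from the Study population section: IVF live birth rate 10% (3/30), margin 0.05, power 80%, alpha 5%, 5% non-evaluable. The one-sided use of alpha comes from the decision rule. Equal true rates of 10% in both arms are my inference; the article does not state them.

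Unadjusted two-proportion formula:

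n per arm = (z₀.₉₅ + z₀.₈₀)² × [p₁(1−p₁) + p₂(1−p₂)] / margin²
= (1.645 + 0.842)² × (0.09 + 0.09) / 0.0025 = 445.1, rounded up to 446.

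Inflation: 446 / 0.95 = 469.5, rounded up to 470 per arm, 940 in total. This matches exactly. With a one-sided alpha of 0.025 the result would be 566, then 596 per arm (1,192), which does not match. The planned size therefore belongs to an unadjusted difference.

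**2. What would stratification change?**

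The documents give no live birth rates by age or follicle number, so every rate here is an assumption. Take a 60/40 age split, equal thirds for two, three and four follicles, and two gradients:

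| Assumed rates (under 40 / 40 and over) | Follicle multipliers | Within-stratum variance / total |
|---|---|---|
| 13% / 5% | 0.6, 1, 1.4 | 0.969 |
| 14% / 4% | 0.5, 1, 1.5 | 0.950 |

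The ratio is Σ w·p(1−p) over the six strata, divided by p̄(1−p̄).

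Power at 10% in both arms with 446 per arm: standard error = √(0.18/446) = 0.0201, and power = Φ(0.05/0.0201 − 1.645) = 80.1%. With variance × 0.97 it is 81.1%, and with variance × 0.95 it is 81.8%. The gain is about 1 to 2 points.

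**3. How often would the two analyses disagree?**

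Simulations used 892 evaluable cycles, six age-by-follicle strata, a mean rate of about 10% and no true difference. They compared the raw bound with a Mantel-Haenszel-weighted bound:

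- Strata balanced between arms: opposite verdicts in about 0.2% (no gradient) to 1.4% of trials.
- Strata not balanced: up to 5.7%.
- Raw bound within 0.25 points of the margin, under the two gradients above: opposite verdicts in 11% to 21% of such trials with balance, and about 40% without.

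Dynamic allocation on center, follicle number and age need not balance every age-by-follicle cell, so the truth may lie between the balanced and unbalanced figures. At a true difference of 5 points, both methods declared non-inferiority in about 5.0% to 5.6% of runs, so both hold their error rate.

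**4. What if all three variables were used as strata?**

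18 × 3 × 2 = 108 cells. 940 / 108 = 8.7 patients per cell, and 8.7 × 0.10 = 0.87 expected births per cell. Full cross-stratification is too sparse to be useful, so an adjusted analysis must say how center is handled. The adjustment sentence names no method.

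**The case against.** The strongest reply is that the text already points to one answer. The second sentence is the specific one: it says how the primary outcome is tested, excludes a model and gives a reason. The decision rule is written as one rate minus the other. The sample size reproduces from the unadjusted formula. On this reading the raw difference is confirmatory, and adjustment serves the secondary outcomes or supportive analyses. That is probably the intention. To reach it, however, the reader must strike the primary outcome from the first sentence or add a label that is not there. The exclusion of a complex model also leaves open whether a simple stratified estimate was the promised adjustment.

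A reader might go further in three directions that the documents do not support.

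- **That the plan gives no guidance on the decisive test.** This is too strong: the evidence above favours the raw difference.
- **That the raw analysis is unsound because balanced allocation argues for adjustment.** Balance on prognostic factors does make an unadjusted standard error somewhat too large, but that is slightly conservative and does not favour a false claim of non-inferiority. At variance ratios of 0.95 to 0.97 the raw interval is only about 1.6% to 2.6% wider (1/√0.97 = 1.016; 1/√0.95 = 1.026). Preferring adjustment is a choice about efficiency and does not correct an error.
- **That the sample size is affected.** It is not.

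It also stands that the power and disagreement figures rest on stratum rates that the documents do not give, and that an analysis plan not shown here may already settle the question.

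**Conclusion.** The contradiction is real, lies in the text and concerns the rule that decides the trial. It does not depend on any calculation. Its practical size is moderate: both candidate analyses are valid, sit on the same risk-difference scale as the margin and would usually agree. Under the assumed gradients the choice is worth about 1 to 2 points of power and changes the verdict in a small percentage of trials, concentrated where the bound falls close to 5%. Those are also the cases where an unranked pair of analyses in an open-label trial would be hardest to defend. Severity: moderate.

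**What to change.** Before analysis, name one confirmatory analysis for the 5% margin and label the other a sensitivity analysis. Either option below resolves the conflict.

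- **Preferred.** Make the confirmatory estimate a Mantel-Haenszel (or stratified Miettinen-Nurminen) risk difference over age group by follicle number (six strata), with its one-sided 95% upper bound. State openly that center, the third stratification variable, is left out because 108 cells would hold about 8.7 patients and fewer than one expected birth each. Report the raw difference as a sensitivity analysis. This stays on the scale of the margin and needs no regression model.
- **Equally acceptable.** Keep the raw difference as the sole confirmatory test, and restrict the adjustment sentence to the secondary outcomes and one named sensitivity analysis of the primary outcome.

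If an analysis plan already makes this choice, bring the protocol wording into line with it. The cost is a wording change: no new data and no change to the 940 cycles.

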### Data circulation

All data from the trial will be compiled in an eCRF. Only people involved in the trial will have access to the data, via a username and a password. No patient identifying information will be stored, and only the first letter of the surname and of the last name will be kept, without any mention of the full name or date of birth. Patient code will be composed of the participating center’s number and another number assigned by that center. Each participating center will store its own data for the duration set by regulation for this type of study under the center’s investigator’s responsibility. Only investigators from Angers University Hospital (AUH) will have access to patient data from other centers on the eCRF. Therefore, for centers that cannot complete patient follow-up at 12 months, patients’ coordinates will be retrieved from the eCRF by AUH investigators and personnel in charge of patient follow-up. At the end of the trial, all data will be deleted. Approval from the CCTIRS (Comité consultatif sur le traitement de l’information en matière de recherche) (Advisory Committee on Treatment of Information in Research in the Field of Healthcare) and the CNIL (Commission nationale informatique et liberté) (National Commission on Informatics and Liberty) have been requested.

### Monitoring and adverse events

We do not expect to have undesirable or serious undesirable events related to the study and its proceedings. Indeed, all procedures included in this study (COS and its monitoring, ovulation trigger, oocyte retrieval, embryo transfer, IUI) are standard procedures and will be performed in accordance with the national guidelines and recommendations. The only part that is specific to our RCT, and that is not considered part of routine practice, is the telephone call that will be made to patients 12 months after enrollment in order to collect information on the evolution of pregnancy. This might be a sensitive topic, especially for couples who did not have a healthy live birth because of pregnancy loss or complications of pregnancy. The personnel in charge of this part will be trained in how to approach the couples and how to deal with the special situations. Moreover, we will have a psychologist available for couples to consult when needed.

All adverse events related to the oocyte retrieval (bleeding, hemoperitoneum, infection, peritonitis, pelvic abscess, etc.) and the anesthesia during the retrieval will be recorded. We will also document whether the complications required any additional treatment, procedure or hospitalization, and add them to the treatment cost.

### Expected repercussions

If LBRs were to be comparable between IVF and conversion to IUI in patients with POR to COS, and if our cost-effectiveness analysis confirms that IUI is indeed more cost-effective, then we would confirm that conversion to IUI is the better treatment option, since it is also less invasive.

## Discussion

This is the first RCT to compare the outcomes of IVF and embryo transfer to conversion to IUI in patients with poor ovarian response (POR) to controlled ovarian stimulation (COS). If our study shows that conversion to IUI is non-inferior to IVF in terms of clinical efficiency and LBR, it would confirm IUI as a better alternative for patients, both individually (less invasive and more patient-friendly) and collectively (lower cost).

## Trial status

The trial already began on 10 January 2018, and participant recruitment and follow-up will continue over a 48-month period, with the anticipated final follow-up telephone call(s) occurring in January 2022. Primary analyses will be complete by June 2022.

## Abbreviations

AFC: Antral follicle count
AMH: Anti-Müllerian hormone
ART: Assisted reproductive treatment
AUH: Angers University Hospital
CCTIRS: Comité consultatif sur le traitement de l’information en matière de recherché = Advisory Committee on Treatment of Information in Research in the Field of Healthcare
CNIL: Commission nationale informatique et liberté = National Commission on Informatics and Liberty
CONSORT: Consolidated Standards of Reporting Trial
COS: Controlled ovarian stimulation
CPR: Clinical pregnancy rate
eCRF: Electronic Case Report Form
ESHRE: European Society of Human Reproduction and Embryology
GA: Gestational age
HCG: Human chorionic gonadotropin
ICER: Incremental cost-effectiveness ratio
ICSI: Intracytoplasmic spermatozoid injection
IUI: Intrauterine insemination
IVF: In vitro fertilization
LBR: Live birth rate
OATS: Oligoasthenoteratospermia
PL: Pregnancy loss
POR: Poor ovarian response
RCT: Randomized controlled trial
